## Safety assessments

### Medical history

A detailed medical history, including a review of all body systems, pre‑ART CD4 counts, and pre‑ART HIV-1 viral load, will be obtained from each subject during the screening visit. Each subject will be questioned by the nurse/study coordinator/investigator/sub-investigator regarding significant past medical history, medical history related to concurrent diseases, concurrent drug use, and drug allergies.

### Physical examination

Physical examination will be performed at screening, week 1, week 4 and week 8 (end of study). Physical examination will include height (only at screening or week 1) and weight and evaluation of the subject’s medical condition. Any new or worsening of medical condition compared to the pretreatment condition (pre-dose on Day 1) should be recorded as an AE on the CRF.

### Vital signs

At screening, week 1, week 4 and week 8 (end of study) vital signs (heart rate, systolic and diastolic blood pressure) will be measured prior to administration of study drug (if applicable) with the subject in the sitting position. Vital signs will be measured after the subject has been sitting at rest for 5 minutes.

### Clinical laboratory tests

Blood samples will be collected (approximately 15 mL) at screening, week 1, week 4 and week 8 (end of study) to measure the following clinical chemistry and hematology parameters: It is important that blood samples are taken before drug administration. Tests will be performed at the local hospital laboratory.

**Chemistry:** Aspartate Transaminase (AST), Alanine Transaminase (ALT), Creatinine, Na, K, C-reactive Protein (CRP), Alkaline phosphatase (ALP), Lactate Dehydrogenase (LD), Albumin, Total Bilirubin, 2-microglobulin, -Glutamyl Transferase.

**Hematology:** Hemoglobin, White blood cell count (WBC) with differential, Platelets.

### HIV viral load (HIV-1 RNA)

A blood sample (approximately 10mL) will be collected in tubes containing EDTA at screening and week 1, week 4 and week 8 (end of study). Tests will be performed at the local hospital laboratory.

# Adverse Event Management

## Non‑serious and serious adverse events

The investigator is responsible for the detection and documentation of events meeting the criteria and definition of an AE or SAE as provided in this protocol (see below). All AEs and SAEs that occur from the time written informed consent is obtained until completion of the study, week 8, will be entered on the appropriate CRF page (see Section 9.1.4). Information to be collected includes the description, date and time of onset, intensity, duration, causality, and outcome of the event. Even if the AE is assessed by the investigator as not reasonably attributable to study drug, its occurrence must be recorded in the source documents and reported on the CRF.

Periodically during the study, after the subject has had an opportunity to spontaneously mention any problems, the investigator should inquire about the occurrence of AEs. The following are examples of open‑ended questions that may be used to obtain this information:

- “How are you feeling?”
- “Have you had any medical problems since your last visit/assessment?”
- “Have you taken any new medicines, other than those given to you in this study, since your last visit/assessment?”

### Definition of an adverse event

An AE is any untoward medical occurrence in a subject administered a pharmaceutical product that does not necessarily have a causal relationship with this treatment.

An AE can therefore be any unfavorable and unintended sign (including an abnormal laboratory finding, for example), symptom, or disease temporally associated with the use of a medicinal product, whether or not considered related to the medicinal product.

Examples of AEs include:

- Exacerbation of a pre‑existing illness following the start of the study
- Increase in frequency or intensity of a pre‑existing episodic event or condition
- Condition detected or diagnosed after study drug administration even though it may have been present prior to the start of the study

An AE **does** **not** include:

- Medical or surgical procedure (e.g., surgery, endoscopy, tooth extraction, transfusion); the condition that leads to the procedure is an AE
- Day to day fluctuations of pre‑existing disease or conditions present or detected at the start of the study that do not worsen
- Situations where an untoward medical occurrence has not occurred (e.g., hospitalizations for cosmetic elective surgery, social and/or convenience admissions)
- The disease or disorder being studied or sign or symptom associated with the disease or disorder unless more severe than expected for the subject’s condition
- Overdose of either study drug or concurrent medication without any signs or symptoms

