# Study objectives AND ENDPOINTS

## Study objectives

### Primary objective

The primary objective of this study is to evaluate the safety of intranasal administration of Vacc-4x with Endocine as adjuvant at three different dose levels.

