## Study endpoints

### Safety endpoints

- AEs recorded at each scheduled and unscheduled visit
- Clinical laboratory evaluations (clinical chemistry, hematology) at screening, week 1, week 4 and week 8 (Termination).
- Viral load (HIV-1 RNA) at screening, week 1, week 4 and week 8 (Termination).
- Physical examinations at screening, week 1, week 4 and week 8 (Termination).
- Vital signs (heart rate, blood pressure) at screening, week 1, week 4, and week 8 (Termination).

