## Inclusion criteria

A subject will be eligible for enrollment in the study if all of the following criteria apply:

- Age above 18 years, both genders.
- HIV positive at least one year.
- Clinically stable on ART for the last 6 months (changes in therapy is allowed as long as the viral load is stable).
- Documented viral load (HIV-1 RNA) less than 50 copies/mL for the last six months.
- Documented stable CD4 cell count ≥ 400x106/L.
- Nadir (lowest ever) CD4 cell count ≥ 200x106/L.
- Signed informed consent.

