### Vaccine toxicity management

#### Administration site reactions

The following local reactions will be reported:

- Pain, tenderness, acute swelling or soreness at the application site (nose). The severity of pain or other reactions will be categorized as: None,’ ‘Mild’ (awareness of symptom but easily tolerated), ‘Moderate’ (discomfort enough to cause interference with usual activities), or ‘Severe’ (incapacitating with inability to work or do usual activity)

For administration site reactions judged to be life-threatening or severe, the investigational drug substance suppliers should be notified within 24 hours, and further vaccines should not be given to the subject prior to consultation with the suppliers.

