### Recording of adverse events and serious adverse events

From the point of signing the informed consent form (ICF) to the first administration of study medication, any worsening of an existing or new medical condition must be recorded on the Medical History CRF page. Following administration of study medication up to the week 8 (Termination), any worsening of an existing or new medical condition must be recorded as an AE on the CRF. The investigator should review all documentation (e.g., hospital progress notes, laboratory, and diagnostic reports) relative to the event being reported. The investigator will then record all relevant information regarding an AE/SAE on the appropriate CRF page. The investigator will evaluate AEs using the following guidelines:

- Description of event (if the event consists of a cluster of signs and symptoms, a diagnosis should be recorded [e.g., flu syndrome] rather than each sign and symptom)
- Onset date and time
- Stop date and time
- Intensity should be described according to the Division of AIDS Table for Grading Severity of Adult and Pediatric Adverse Events, December 2004 (Appendix 16.1) as MILD (Grade 1), MODERATE (Grade 2), SEVERE (Grade 3), or life threatening (Grade 4). Intensity is defined as one of the following:
- Mild: transient or mild discomfort; no limitation in activity; no medical intervention/therapy required
- Moderate: mild to moderate limitation in activity- some assistance may be needed; no or minimal medical intervention/therapy required
- Severe: marked limitation in activity, some assistance usually required; medical intervention/therapy required, hospitalizations possible
- Life-threatening: extreme limitation in activity, significant assistance required; significant medical intervention/therapy required; hospitalization or hospice care probable

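### Section 9.1.1 keeps HIV-associated symptoms out of the AE definition unless they exceed what is expected, while 8.3.2 and 9.1.4 record every new or worsened condition; the rules conflict for a narrow group of lower-grade systemic events

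*Protocol*

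**What the plan says.** Section 9.1.1 starts broadly. An AE can be any unfavourable sign, "symptom, or disease temporally associated with the use of a medicinal product, whether or not considered related to the medicinal product". Its examples include exacerbation of an illness the subject already had. It then lists what is not an AE, including "The disease or disorder being studied or sign or symptom associated with the disease or disorder unless more severe than expected"; the sentence goes on to tie the expectation to the subject's own condition. A separate bullet excludes day-to-day fluctuation in pre-existing conditions that do not get worse.

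Two other sections set a recording rule with no exception for HIV:

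- Section 9.1.4, from first administration to week 8: "any worsening of an existing or new medical condition must be recorded as an AE on the CRF".
- Section 8.3.2: "Any new or worsening of medical condition compared to the pretreatment condition (pre-dose on Day 1) should be recorded as an AE".

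The objective in Section 3.1.1 reads: "The primary objective of this study is to evaluate the safety of intranasal administration of Vacc-4x with Endocine as adjuvant", at three dose levels. The first safety endpoint in Section 3.2.1 is "AEs recorded at each scheduled and unscheduled visit". Neither it nor any other endpoint is designated primary.

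**The concern.** An investigator who sees new fatigue or mild fever after a dose has two instructions. Sections 8.3.2 and 9.1.4 say to record it. Section 9.1.1 allows it to be left off if it is thought to belong to the HIV infection and not to exceed what was expected. The protocol does not define expected, so the choice is one of judgement.

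The order of steps makes this matter. Section 9.1.4 has a cautious causality rule: unless a causal link can be excluded, the event is at least possibly related. An event set aside under the definition in 9.1.1 never reaches that step, so attribution to HIV takes the place of the causality assessment. It is then absent from the AE summaries in Section 11.6.2 and cannot be restored at analysis.

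**Working it through.** **Step 1. Set the rules side by side for events after the first dose.**

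| Event | 9.1.1 | 8.3.2 and 9.1.4 | Result |
| --- | --- | --- | --- |
| Background complaint, unchanged | Not an AE (fluctuation bullet) | Not an AE | Agree |
| New or worse, not ascribed to HIV | AE | AE | Agree |
| New or worse, ascribed to HIV, judged beyond expectation | AE | AE | Agree |
| New or worse, ascribed to HIV, judged within expectation | Not an AE | AE | Conflict |

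Only the last row conflicts. The first row shows that the disease bullet is not needed to keep stable complaints out.

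**Step 2. Does another section settle the last row?**

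- Section 9.1 requires events judged unrelated to study drug to be recorded, but only if they already meet the AE definition. It does not decide whether they do.
- Section 5.4.1 requires nasal application-site reactions to be reported, with no HIV exception. These fall outside the conflict.
- Section 5.4.1 also requires systemic reactions to be graded. It does not say that a symptom excluded under 9.1.1 must still be entered, and supplier contact is required only for Grade 3 or 4 reactions thought related.
- The SAE definition in Section 9.1.2 does not repeat the exclusion, so serious events are covered.
- Viral load and CD4 counts are measured at screening and weeks 1, 4 and 8, whatever is recorded as an AE.

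What is left is non-serious, mainly lower-grade, non-specific systemic symptoms.

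**Step 3. Scale.** The protocol gives no figure to reproduce. The one input from it is 6 subjects per arm (Section 11.1).

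- One omitted event changes an arm's incidence by 1/6 = 16.7 percentage points. For example, 1/6 (exact 95% CI 0.4% to 64.1%) becomes 0/6 (0% to 45.9%).
- Under Section 4.1, the first five subjects comprise three on the lowest dose and two on adjuvant alone, and the next level follows a two-week safety evaluation. One omission there is 1/3 of the vaccinated subjects. This assumes that the evaluation draws on recorded AEs, which the section does not state.

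**Step 4. Illustration, on assumed rates.** Let p be the true proportion of subjects with such a symptom and s the share left out. The chance that an arm of 6 records at least one is 1 − (1 − p(1 − s))^6.

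| Assumed p | s = 0 | s = 0.25 | s = 0.5 |
| --- | --- | --- | --- |
| 10% | 0.469 | 0.374 | 0.265 |
| 20% | 0.738 | 0.623 | 0.469 |
| 30% | 0.882 | 0.783 | 0.623 |

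For p = 10% and s = 0.5: 1 − 0.95^6 = 0.265. Neither p nor s comes from the protocol.

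**The case against.** The strongest reply is that the exception within the bullet does most of the work. Section 5.2 requires "Documented viral load (HIV-1 RNA) less than 50 copies/mL for the last six months", clinical stability on ART and a stable CD4 count of at least 400 × 10^6/L; Section 5.3 excludes a recent AIDS-defining illness. In such subjects hardly any HIV symptom is expected, so a new one would usually exceed expectation and count as an AE under all three sections. The examples in 9.1.1 also lean towards recording. This stands, and it is why the affected group is narrow. It does not remove the conflict: the threshold is undefined, and if almost everything passes it, the bullet has little legitimate use in this trial.

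A reader might infer that vaccine reactions in general can be dropped from a primary safety endpoint. The protocol does not support that. The reactions it expects most often are nasal, and these are reported separately; AEs are one of five safety endpoints, and none is called primary. A reader might also infer that worsening HIV disease would go unseen, but viral load and CD4 are measured independently. Finally, one might infer a spurious protective difference from omission in a vaccine arm and not in the control. The protocol does not say who is blinded, so equal omission cannot be taken for granted, but nothing in it shows unequal omission either.

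A last objection is that recording every symptom would clash with other rules. That is fair, and the wording of the fix has to respect it.

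**Conclusion.** The contradiction is in the current text and should be resolved. It is limited to new or worsened, mainly lower-grade systemic symptoms that an investigator attributes to HIV and considers expected. For these, an undefined judgement can replace the causality assessment in a trial whose primary objective is safety.

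The only size that follows from the protocol is the weight of a single event: 16.7 percentage points in an arm of 6. How often omission would occur, and whether it would differ by arm, is unknown; the illustrative probabilities rest wholly on assumed rates. The text shows room for omission, not that any will happen. This is a modest correction, worthwhile because an event never recorded cannot be recovered later.

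**What to change.** Reconcile 9.1.1 with 8.3.2 and 9.1.4 in one of two ways:

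- delete the bullet on the disease under study; or
- state that any medical condition that is new or worse than the pre-dose Day 1 state is an AE whatever its presumed link to HIV, and that this link is entered in the causality assessment.

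Keep three existing rules: the bullet on pre-existing conditions that do not worsen, the instruction in 9.1.4 to enter a diagnosis in place of its component symptoms, and the rule in 9.1.3 on when laboratory values go on the AE page. Framing the new sentence around conditions, not every sign or symptom, avoids a clash with the last two.

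The cost is one bullet or one sentence, plus a few more AE records, some of them background complaints. The randomised Endocine-only arm puts those in context. The change affects recording only.

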### Definition of a serious adverse event

An SAE is any untoward medical occurrence that at any dose:

- Results in death
- Is life-threatening

*Note:* The term “life‑threatening” in the definition of “serious” refers to an event in which the subject was at risk of death at the time of the event; it does not refer to an event which hypothetically might have caused death if it were more severe.

- Requires inpatient hospitalization or prolongation of existing hospitalization

*Note:* Complications that occur during hospitalization are AEs. If a complication prolongs hospitalization or fulfills any other serious criteria, the event is serious. Hospitalization for elective treatment of a pre‑existing condition that did not worsen from the pretreatment assessment is not considered to be an AE.

- Results in persistent or significant disability/incapacity

*Note:* The term disability means a substantial disruption of a person’s ability to conduct normal life functions. This definition is not intended to include experiences of relatively minor medical significance such as uncomplicated headache, nausea, vomiting, diarrhea, influenza, or accidental trauma (i.e., sprained ankle) that may interfere or prevent everyday life functions but do not constitute a substantial disruption.

- Is a congenital anomaly/birth defect
- Important medical events that may not be immediately life‑threatening or result in death or hospitalization but may jeopardize the subject or may require intervention to prevent one of the outcomes listed in the definition above should also usually be considered serious.

*Note:* Examples of such events are intensive treatment in an emergency room or at home for allergic bronchospasm, blood dyscrasias, or convulsions that do not result in hospitalization; or development of drug dependency or drug abuse.

### Clinical laboratory abnormalities and other abnormal assessments

Laboratory abnormalities are usually not recorded as AEs or SAEs. All abnormal laboratory values judged to be at least possibly drug related or clinically significant abnormal laboratory results of any causality not associated with the disease under study must be repeated. The investigator will exercise medical judgment in deciding whether abnormal laboratory values are clinically significant. In some cases, significant changes within the range of normal will require similar judgment by the Investigator.

Clinically significant abnormal laboratory values should not be listed on the AE page of the CRF unless clinical signs or symptoms are present. If an abnormal laboratory value or assessment is clearly related to a medically defined diagnosis or syndrome, the diagnosis or syndrome will be recorded on the AE page, not the individual laboratory values.

All clinically significant abnormal laboratory results or assessments will be followed until they resolve (return to normal or pretreatment values) or stabilize, or until they are judged by the investigator to be no longer clinically significant.

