#### Adverse events

For presentation, AE verbatim text will be coded into a Medical Dictionary for Regulatory Activities Terminology (MedDRA) term, and classified by System Organ Class (SOC) and preferred term prior to analysis. AEs will then be summarized and grouped by SOC and preferred term. AEs with onset on or after the start of study medication are considered treatment emergent. AEs reported prior to treatment administration will be reported separately from treatment emergent AEs. A cross reference listing, which will relate SOC, preferred term, and verbatim text will be provided.

In addition, summaries will be provided by incidence, severity (mild, moderate, severe), and relationship to study medication (Related, Unrelated). "Possibly Related," "Probably Related," and "Definitely Related" will be grouped as “Related.”

SAEs and AEs leading to discontinuation will be summarized and listed.

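### The AE rules behind the primary safety objective are inconsistent: asymptomatic laboratory abnormalities are kept off the AE page even if judged drug related, and the severity summary omits Grade 4

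*Protocol*

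**What the plan says.** Protocol Section 3.1.1 makes safety the trial's main aim: "The primary objective of this study is to evaluate the safety of intranasal administration of Vacc-4x with Endocine as adjuvant at three different dose levels". Section 3.2.1 lists five safety endpoints without ranking them. The first is "AEs recorded at each scheduled and unscheduled visit"; laboratory evaluations are another.

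**Laboratory findings.** Section 9.1.1 defines an AE to include "any unfavorable and unintended sign (including an abnormal laboratory finding, for example), symptom, or disease temporally associated with the use of a medicinal product". Its list of things that are not AEs does not mention asymptomatic laboratory findings. Section 9.1 requires all AEs to be entered, including those the investigator does not attribute to study drug. Section 9.1.3 opens by saying that laboratory abnormalities are not usually recorded as AEs or SAEs, and later adds: "Clinically significant abnormal laboratory values should not be listed on the AE page of the CRF unless clinical signs or symptoms are present". Where a value clearly belongs to a diagnosis or syndrome, that diagnosis goes on the AE page.

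**Severity.** Section 9.1.4 grades intensity as "MILD (Grade 1), MODERATE (Grade 2), SEVERE (Grade 3), or life threatening (Grade 4"). Section 11.6.2, under Adverse events, says "summaries will be provided by incidence, severity (mild, moderate, severe), and relationship to study medication".

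**Pre-dose events.** Section 9.1 collects AEs from consent on the appropriate CRF page and refers to Section 9.1.4 for which page that is. Section 9.1.4 says that new or worsening conditions before the first dose "must be recorded on the Medical History CRF page". Section 11.6.2 says "AEs reported prior to treatment administration will be reported separately from treatment emergent AEs".

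**The concern.** AE counts carry much of the answer to the primary objective, so what enters the AE page, and how it is then tabulated, should be fixed without ambiguity. Here two investigators could follow two sections of the same protocol and produce different AE counts from the same patient.

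The laboratory rule matters most because it governs collection. Causality, action taken and outcome are specified only for AE records (Section 9.1.4). If an asymptomatic abnormality is kept off the AE page, those judgements have no stated place on the CRF, and no later analysis plan can recover them. The Grade 4 gap concerns presentation: the most severe category recorded has no place in the planned severity summary.

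**Working it through.** The protocol states no figure on this point, so the check is a comparison of the sections, followed by a note on scale.

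**1. Follow one event through the rules.** Take a laboratory abnormality that is clinically significant, judged possibly drug related, without signs or symptoms, and not part of a diagnosis.

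| Step | Section | Result |
| --- | --- | --- |
| Is it an AE? | 9.1.1 | It can be: laboratory findings are included and not excluded later |
| Must it be entered? | 9.1 | Yes, with intensity, causality and outcome |
| Does it go on the AE page? | 9.1.3 | No, because there are no signs or symptoms |
| What happens to it? | 9.1.3 | Repeated, then followed until resolved, stable or no longer significant |
| Is it in the AE tables, including related AEs? | 11.6.2, Adverse events | No |
| Is it in the laboratory tables? | 11.6.2, Vital signs and laboratory parameters | Yes: change from baseline, shift to worst severity and, if out of range, the out-of-range summary |
| Are causality, action and outcome tabulated there? | 11.6.2, same heading | No |

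Sections 9.1 and 9.1.1 therefore give one answer and Section 9.1.3 another. The value is still analysed, but not the judgement that it may be drug related.

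**2. Compare the severity scales.** Section 9.1.4 has four levels and Section 11.6.2 has three: 4 − 3 = 1 level without a category, namely life-threatening. The SAE listing covers this only in part. Section 9.1.4 itself says that severity and seriousness are different things. It describes Grade 4 by extreme limitation of activity and probable hospitalization, whereas the life-threatening criterion in Section 9.1.2 requires that the subject was at risk of death at the time. A Grade 4 event need not meet a seriousness criterion.

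**3. Trace the pre-dose events.** Section 9.1 calls events from consent onward AEs and asks for intensity and causality, and Section 7.3.1 lists AEs at screening. Section 9.1.4 names only the Medical History page for this period. Section 11.6.2 plans a separate report of pre-treatment AEs. Whether that report is to draw on the Medical History page is not stated.

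**4. Scale only.** Inputs: 6 subjects per arm (Section 11.1) and three vaccine arms, so 3 × 6 = 18 vaccinated.

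- One event in one arm: 1/6 = 16.7 percentage points.
- One event among the vaccinated: 1/18 = 5.6 percentage points.
- Exact (Clopper-Pearson) 95% intervals: 0/6 gives 0 to 45.9%; 1/6 gives 0.4 to 64.1%; 0/18 gives 0 to 18.5%; 1/18 gives 0.1 to 27.3%.

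These figures show the weight of a single event. They do not forecast how many would be left out.

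**The case against.** The best defence is that Section 9.1.3 is the specific recording rule and qualifies the general definition, which says only that an AE can be a laboratory finding. Laboratory evaluations are a safety endpoint in their own right, with out-of-range summaries and shifts to worst severity. Values thought drug related must be repeated, and clinically significant ones followed. Much of this stands. A reader might infer that asymptomatic laboratory toxicity is lost to the safety analysis, and the protocol does not support that: values and severity are tabulated, and the diagnosis or syndrome exception narrows the gap further. What the defence leaves unanswered is that causality, action and outcome have no specified place once the AE page is closed to the event.

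On Grade 4, a reader might infer that life-threatening events would vanish. They would not. Those meeting a seriousness criterion are summarised and listed as SAEs, and nothing says that Grade 4 records are dropped. A statistical analysis plan could add the row. But the protocol lists the categories itself and omits one that it collects.

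On pre-dose events, a reader might infer that the protocol sends them to two different pages. It does not: Section 9.1 defers to Section 9.1.4, which names one. Only the source of the planned report is unclear.

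It is also fair to say that 16.7 points per event holds for any event in any arm of 6, that the sample size was chosen for descriptive statistics, and that no stated AE threshold or test depends on these counts. A claim that an arm would read 0/6 when the truth is 1/6 or 2/6 would be hypothetical.

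**Conclusion.** The point holds as two inconsistencies and one minor ambiguity, and should be corrected.

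- **Laboratory findings:** Sections 9.1 and 9.1.1 conflict with Section 9.1.3. An asymptomatic abnormality without a linked diagnosis, even one judged drug related, stays in the laboratory tables but has no recorded causality, action or outcome and cannot enter the related-AE summary.
- **Severity:** four grades are recorded and three are summarised. The SAE listing fills the gap only in part.
- **Pre-dose events:** the CRF source of the pre-treatment AE report is not clear. Treatment-emergent results are unaffected.

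The effect on results cannot be estimated, because the protocol gives no expected rate of laboratory or Grade 4 events. The per-event figure of 16.7 points in an arm of 6 indicates scale and nothing more. The conclusion assumes that investigators follow Section 9.1.3 as written and that no other form collects causality for laboratory values; the protocol mentions none. The protocol has a primary safety objective and unranked safety endpoints, so this should not be described as a defect in a designated primary endpoint.

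**What to change.** 1. Reconcile Sections 9.1.1 and 9.1.3 so that laboratory abnormalities judged clinically significant, or at least possibly drug related, are recorded as AEs with grade and causality whether or not symptoms are present. Section 9.1.3 already uses both categories, so no new laboratory threshold is needed. The rule that a diagnosis is entered in place of its individual values can stay.
2. Add life-threatening (Grade 4) to the severity summary in Section 11.6.2, so that it matches the scale in Section 9.1.4.
3. Name one CRF source for pre-dose events and use it for the pre-treatment report, with Sections 9.1, 9.1.4 and 11.6.2 worded alike.

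The cost is protocol and CRF-guideline wording. The first change brings a few more AE records and slightly higher reported AE rates, which may look less favourable. The second adds one category to a table, and the third does not touch the treatment-emergent results.
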